## **Trial design {8}**

Stepped Wedge Cluster Randomized Controlled Trial. The 7 agencies were randomized: 4 agencies (and 12 sites that operate under them) and 3 agencies (and 11 sites that operate under them) were randomized to Wedge 1 and Wedge 2, respectively.

## **Methods: Participants, interventions and outcomes**

### **Study setting {9}**

7 Head Start agencies across New York State were randomized to implement interventions in either Fall 2018 or Winter/Spring 2019

### **Eligibility criteria {10}**

From March thru September 2018 Head Start staff recruited a) English and/or Spanish speaking parents, b) of children 3 years of age on/about September 2018, c) who planned to remain at the site through the school year.

### **Who will take informed consent? {26a}**

Head Start staff obtained informed consent

### **Additional consent provisions for collection and use of participant data and biological specimens {26b}**

NA- the only study data were de-identified demographics from agencies and parent-completed surveys regarding their child's sleep and their knowledge, attitudes, self-efficacy and beliefs about child sleep.

## **Interventions**

### **Explanation for the choice of comparators {6b}**

NA- cross-over design

### **Intervention description {11a}**

The study was implemented across the 2018-2019 school year. Head Start staff in each Wedge received half-day trainings one month prior to implementing the ECSEP's 1-hour Parent Workshop and 2-week classroom curriculum, and the Sleep Health Flipchart guided discussion. See Table 1:

Table 1: Intervention Descriptions: Content, Delivery and Materials

| Early Childhood Sleep Education Program (ECSEP) TM                      |                                                                                                                                                                                                                               |                                                                                                                                                                                                         |                                                                                                                                                                                                                                                                                                                                                                                                           |
|------------------------------------------------------------------------------------|-------------------------------------------------------------------------------------------------------------------------------------------------------------------------------------------------------------------------------|---------------------------------------------------------------------------------------------------------------------------------------------------------------------------------------------------------|-----------------------------------------------------------------------------------------------------------------------------------------------------------------------------------------------------------------------------------------------------------------------------------------------------------------------------------------------------------------------------------------------------------|
|                                                                                    | Content:                                                                                                                                                                                                                      | Delivery:                                                                                                                                                                                               | Materials:                                                                                                                                                                                                                                                                                                                                                                                                |
| Parent Workshop (ECSEP)                                                     | 
 
• Science or sleep
 
• Sleep effects on child's brain & body
 
• Hours of sleep needed
 
• Bedtime routines (why, 'how to')
 
                        | 
 
• Held at sites
 
• During parent meeting
 
• 1-week before class lessons
 
                                                               | 
 
• 1-hour power-point
 
• Parents receive take-home guide
 
                                                                                                                                                                                                                                                                                         |
| Classroom Lessons (ECSEP)*                                                  | 
 
• Why children need sleep, bedtime routine steps, etc.
 
• Modalities: songs, storybooks, teddy bears to model bedtime routines
 
                                      | 
 
• By Head Start teachers
 
• Lessons: 8 sessions over 2 weeks, 40 min//day
 
• Small & large group activity
 
                         | 
Child take-homes:
 
 
• Teddy Bear (2nd week)
 
• Book (read in class)
 
• Toothbrush & toothpaste
 
• Sticker chart & stickers
 
 
Teacher tools:
 
 
• Curriculum guide, lesson plans, 3 classroom bears, 10 enrichment lessonsb
 
 |
| Multimedia Materials Developed During Pre-Implementation                           |                                                                                                                                                                                                                               |                                                                                                                                                                                                         |                                                                                                                                                                                                                                                                                                                                                                                                           |
|                                                                                    | Content:                                                                                                                                                                                                                      | Delivery:                                                                                                                                                                                               | Materials:                                                                                                                                                                                                                                                                                                                                                                                                |
| Sleep Health Flipcharta
(Parent 1-to-1 with Head Start Staff) | 
 
• Reviews Parent Workshop content
 
• Additional tailored content on:
 
• FAQs: night-waking, co-sleeping etc.
 
• Red flags: snoring, daytime fatigue
 
 | 
 
• At home or Head Start site
 
• During routine 1-to-1 visits
 
• Guides staff & parent dialogue
 
• Duration: 20-25 minutes
 
 | 
 
• Spiral-bound, desk-sized, full color
 
• 26 pages: 13 parent- and
 
• 13 staff-facing
 
• English and Spanish
 
                                                                                                                                                                                                                    |
| Sleep Health Brochure                                                       | 
 
• Summarizes Flipchart content
 
• Includes: bedtime 'do's & don'ts
 
• Sleep Goals: parents can write 1-3
 
                                                | 
 
• Parent receives after Flipchart sessions
 
                                                                                                            | 
 
• Tri-fold brochure
 
• English and Spanish
 
                                                                                                                                                                                                                                                                                                      |
| Bedtime Challenges Brochure*                                                | 
 
• Strategies for: fighting bedtime, night-time fears, shared sleep space, etc.
 
                                                                                              | 
 
• Parent receives after Flipchart sessions
 
                                                                                                            | 
 
• 1-page, double-sided
 
• English and Spanish
 
                                                                                                                                                                                                                                                                                                   |
| Sleep Health Video*                                                         | 
 
• Professional production, content mirrors above materials
 
                                                                                                                  | 
 
• Shared via agency social media, website, newsletter,
 
                                                                                                | 
 
• 8-minute video distributed as .mp4
 
• English and Spanish
 
                                                                                                                                                                                                                                                                                     |

a One agency delivered the Sleep Health Flipchart in small groups immediately after the 1-hour Parent Workshop

b Supplemental lessons for future use; not implemented during trial

## Criteria for discontinuing or modifying allocated interventions {11b}

NA- no changes were made.

## Strategies to improve adherence to interventions {11c}

NA- There were no particular strategies to promote adherence to the classroom curriculum as children were present on site for the lessons. Regarding strategies to promote attendance at the 1-hour parent workshop, the event was held during times convenient for families, and some sites served refreshments.

## Relevant concomitant care permitted or prohibited during the trial {11d}

NA- there was no other sleep education provided or prohibited.

## Provisions for post-trial care {30}

NA- there was no follow-up beyond the 12 month (follow-up 4) survey data.

## Outcomes {12}

Outcomes were parent-reported school-night sleep duration per sleep logs (primary: at 9 months; secondary: at 12 months), mild/moderate sleep difficulties per validated questionnaire, and KASB total and domain scores at 9 and 12 months (secondary)

## Participant timeline {13}

|         |                 |                                     |                                    | Control                             | Intervention                       |                       |
|---------|-----------------|-------------------------------------|------------------------------------|-------------------------------------|------------------------------------|-----------------------|
| Wedge 1 | April-Sept KASB | Sept 2018                           | Nov 2018                           | Jan 2019                            | Mar 2019                           | Sept 2019             |
|         | Baseline        | Baseline                            | Follow-Up Data 1                   | Follow-Up Data 2                    | Follow-Up Data 3                   | Follow-Up Data 4      |
|         |                 | 1-week before Wedge 1 Interventions | 1-week after Wedge 1 Interventions | 1-week before Wedge 2 Interventions | 1-week after Wedge 2 Interventions | 1 Year after Baseline |
|         | KASB TAYSIDE    | Log                                 | Log KASB TAYSIDE                   | Log                                 | Log KASB TAYSIDE                   | Log KASB TAYSIDE      |
|         | KASB TAYSIDE    | Log                                 | Log KASB TAYSIDE                   | Log                                 | Log KASB TAYSIDE                   | Log KASB TAYSIDE      |

Figure 2

## Sample size {14}

Mean school night sleep duration at **FU3 (app. 9 months)** was the primary outcome. Clinically significant effects are evident from an additional 30-35 minutes of nighttime sleep. With 7 agencies, a sample of n=173 provides 90% power to detect a difference as small as 15 minutes between Intervention vs. Control phases ( $p < .05$ , 2-tail). For parent KASB, a secondary outcome, a sample of n=450 provides >97% power to detect a moderate effect size (Cohen's  $d = 0.3$ ) for each of its named scales.

## Recruitment {15}

There were no specific strategies to reach each agency's targeted recruitment goal.

## Assignment of interventions: allocation

### Sequence generation {16a}

Randomization was at the agency level. The 7 agencies were randomly assigned by a computer to implement interventions in Fall 2018 (Wedge 1) or Spring 2019 (Wedge 2)

### Concealment mechanism {16b}

NA- this was infeasible as sites needed to prepare to implement the intervention in Fall 2018 or Spring 2019.

### Implementation {16c}

As noted above, the study statistician generated the allocation of the 7 agencies to either Wedge 1 or Wedge 2.

## Assignment of interventions: Blinding

### Who will be blinded {17a}

NA- see above. Sites and families were cognizant of when the intervention(s) were offered.

### Procedure for unblinding if needed {17b}

NA- see above..

## Data collection and management

### Plans for assessment and collection of outcomes {18a}

During these 2.5 years, the study team and partners developed and piloted intervention materials and built Head Start capacity to enroll participants, deliver interventions and collect study data. A kick-off retreat in March 2018, just prior to recruitment, was held to review logistics and materials. Researchers trained agency staff to enroll families and administer study instruments. About one month prior to each site's implementation of interventions, developers of the ECSEP™ (Sweet Dreamzzz, Inc., now part of Pajama Program) provided half-day trainings to staff delivering the Parent Workshop, Classroom Lessons and Sleep Health Flipchart .

*Child Sleep Duration*- This was measured from sleep log data for school nights (Sunday through Thursday). At recruitment, agency staff showed parents how to record their child's bed- and wake-times, defined as "lights out" and "when the child woke up to start the day," respectively. Parents then completed 7-day paper-and-pencil sleep logs at 5 points: 1 week before/after implementation in Wedges 1 and 2, and at final 1-year follow-up (FU4).

*Child Sleep Difficulties*: This was assessed with the Tayside Children's Sleep Habits Questionnaire (Tayside). This valid and reliable 10-item tool assesses difficulties initiating and maintaining sleep in 1-5 year olds. This low literacy (<= 6th grade) questionnaire is used in research. For this RCT we reduced the recall period to 2 months (from 3), and edited language for clarity (e.g., double negatives). The first nine items were each scored from 1-4; a total score of  $\geq 8/36$  indicates mild/moderate difficulties.

*Parent Knowledge/Attitude/Self-efficacy/Beliefs (KASB) Questionnaire*: The KASB Questionnaire reflects content from the ECSEP Parent workshop regarding child sleep across the named domains. Parents rate agreement with 27 items on a 5-point scale for Knowledge (n=12); Attitudes (n=5); Self-efficacy (n=8) and Beliefs (n=2). One multiple-choice item asks how much sleep a preschooler requires.

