### Objectives {7}

This was a primary prevention trial of sleep health interventions in Head Start. This RCT of multi-level interventions grounded in the social-ecological model examined the following outcomes at ~9- and 12-month follow-up: a) child sleep duration, b) child sleep difficulties, and c) parent knowledge, attitudes, beliefs, and self-efficacy (KASB) regarding children's sleep.

-SLEEP DURATION (CHILD): Hypothesized differences in sleep duration for Intervention vs. Control periods were: a) longer duration for Intervention periods (Primary Outcome: difference at FU3 [app. 9 month follow-up]), b) >30-minute difference at FU3, and c) a 15-minute difference in duration at FU4 (app. 12 months). Sleep duration was measured via parent-reported sleep logs.

-SLEEP DIFFICULTIES (CHILD): Hypothesized differences between Intervention vs. Control periods were: a) lower mean total scores, b) lower odds of scores  $\geq 8/36$  and c) fewer parents reporting a sleep problem in the 10th Tayside item (Yes/No). Surveys with at least 7 of 9 items scored were included in analysis. The Tayside Children's Sleep Habits Questionnaire was used to assess this outcome. (Secondary outcome)

-KNOWLEDGE-ATTITUDES-SELF EFFICACY- BELIEFS (PARENT): Hypothesized differences in parents'

KASB for Intervention vs. Control periods were: a) higher KASB total scores and b) higher scores for each domain. KASB scales with at least 80% non-missing responses were included in analysis. The KASB survey was developed to align with the main educational intervention, the Early Childhood Sleep Education Program. (Secondary outcome)

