## **Statistical methods**

### **Statistical methods for primary and secondary outcomes {20a}**

#### **STATISTICAL ANALYSIS PLAN**

Summary statistics of continuous variables were calculated as means and standard deviations; frequency distributions (n and %) are shown for discrete variables. To analyze treatment effect we fitted multi-level generalized linear models with the study outcome variables as dependent variables, an indicator for post-intervention status, indicators for the study phase (follow-ups 1 through 4, baseline as reference category), and covariates to adjust for age, child sex, Hispanic ethnicity, and race. Random intercepts at the agency and participant levels were included. For continuous outcomes (sleep duration, questionnaire scale scores) the identity link and gaussian error family were used. The coefficient of the post-intervention indicator is the estimate of the average treatment effect and is presented along with its 95% confidence interval (CI). For the dichotomous outcomes (positive Tayside questionnaire, parent-reported sleep problem), the log link and logistic error family were used. In this model the treatment is the odds ratio (exponentiated coefficient) of the post-intervention indicator, presented with its 95% CI.

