### **Methods in analysis to handle protocol non-adherence and any statistical methods to handle missing data {20c}**

NA- there was no such protocol

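### As printed, nine Tayside items scored 1–4 and a cut-off of ≥8/36 are incompatible: every survey with 8 or 9 items answered is positive, so the odds ratio for hypothesis (b) would be uninformative

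*Combined protocol and SAP*

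**What the plan says.** Plans for assessment and collection of outcomes {18a} gives the scoring: "The first nine items were each scored from 1-4". The same sentence says that a total of 8 or more out of 36 "indicates mild/moderate difficulties".

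Objectives {7} sets three hypotheses for child sleep difficulties, comparing Intervention with Control periods: (a) a lower mean total; (b) "lower odds of scores" at or above the same 8/36 cut-off; (c) fewer positive answers to the separate yes/no tenth item. It labels the outcome secondary and adds an inclusion rule: "Surveys with at least 7 of 9 items scored were included in analysis".

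The Statistical Analysis Plan covers (b) and (c) together: "For the dichotomous outcomes (positive Tayside questionnaire, parent-reported sleep problem), the log link and logistic error family were used". The effect is reported as the odds ratio of the post-intervention indicator, with a 95% confidence interval.

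On missing data, section {20c} says only "NA- there was no such protocol". No section gives another item range, a recoding to zero, or a rule for forming the total when 7 or 8 items are answered.

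**The concern.** A cut-off is useful only if scores can fall on both sides of it. Here the lowest score that a complete survey can reach is already above the cut-off. If the printed rules were applied, a child with no sleep difficulty on any item would be classed as having mild/moderate difficulties, before and after the intervention alike.

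At stake is the interpretation of the odds ratio for a positive Tayside questionnaire. Under the printed rules there is no outcome variation among surveys with 8 or 9 items answered, and so no odds ratio to estimate from them. If a sensible odds ratio was obtained from such surveys, it came from a coding or a cut-off that the plan does not state, and a reader could neither reproduce nor interpret it.

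A second, smaller question follows from the inclusion rule. With a fixed cut-off and no stated rule for incomplete totals, the class given to a survey may depend on how many items the parent answered.

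**Working it through.** **Inputs.** Nine scored items, each 1 to 4, and a cut-off of 8 or more out of 36 (section {18a}); the same cut-off, and a minimum of 7 answered items (Objectives {7}). No power, alpha or standard deviation enters.

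**Step 1: the plan's own figure.** Maximum total = items × highest score = 9 × 4 = 36. This reproduces the stated denominator.

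**Step 2: the lowest possible total.** Minimum = items answered × lowest score. All response patterns under 1–4 scoring were counted:

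| Items answered | Range of raw total | Patterns | Raw total below 8 | Below 8 after scaling to nine items |
|---|---|---|---|---|
| 9 | 9 to 36 | 4^9 = 262,144 | 0 | 0 |
| 8 | 8 to 32 | 4^8 = 65,536 | 0 | 0 |
| 7 | 7 to 28 | 4^7 = 16,384 | 1 | 0 |

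The single exception has seven items answered, all scored 1, with raw total 7. On the nine-item scale it becomes 7 × 9/7 = 9 and is positive too. These are counts of possible patterns, not estimates of how often each would occur.

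**Step 3: can the documents tell which figure is wrong?** Two other codings were tried, purely as assumptions.

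- Items 0–4: maximum 9 × 4 = 36, minimum 0; 10,945 of 1,953,125 complete patterns fall below 8. This fits the denominator and lets the cut-off work, but it needs five response options, whereas 1–4 has four.
- Items 0–3 (the printed four options shifted to start at zero): maximum 9 × 3 = 27, which contradicts the stated 36.

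So a maximum of 36 fits both 1–4 and 0–4 and does not settle the matter.

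**Step 4: incomplete surveys.** Suppose that the cut-off stays at 8 and raw totals are used.

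- Eight items: a raw total of 7 scales to 7 × 9/8 = 7.875, still below 8, and a raw total of 8 scales to 9. Scaling never changes the class.
- Seven items: a raw total of 7 scales to 9 and changes class; a raw total of 6 scales to 6 × 9/7 = 7.71 and does not.

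Only seven-item surveys with a raw total of exactly 7 are sensitive to the rule. Under 1–4 scoring that is 1 pattern of 16,384. Under the assumed 0–4 scoring it is 3,180 − 1,660 = 1,520 of 78,125. The documents give no item non-response rate, so the number of real surveys involved is unknown.

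**The case against.** The strongest reply is that this is a reporting slip. The document was written after the event: the auditing section says that the trial is over, and the analysis plan describes models already fitted. An outcome that was almost constant should have been noticed at fitting, so the analysed coding may well have been sound and one of the printed figures wrong. That stands as a possibility. It does not remove the point, because the same cut-off is printed in two sections, the item range is plain, and nothing else in the documents resolves the conflict.

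The reply is also right on scope. The cut-off drives one of three hypotheses. The mean total score and the tenth yes/no item do not use it. Nor does sleep duration: "Mean school night sleep duration at FU3 (app. 9 months) was the primary outcome". The Abstract does list sleep difficulties among primary outcomes, but Objectives {7} labels them secondary.

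Three stronger readings are tempting, and the documents do not support them:

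- **That the analysed binary outcome carried no information.** This holds only if the printed range and the printed cut-off were both applied, which the documents do not show.
- **That a zero-based range is the correct coding.** This would be a statement about the instrument's scoring, which the documents do not reproduce; Step 3 shows that zero-based coding does not fit cleanly either.
- **That totals were left unprorated.** The plan is silent. The fault is the missing rule, not a wrong one.

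**Conclusion.** The point holds for the plan as printed. With nine items scored 1–4, all surveys with 8 or 9 items answered are positive in both periods. The one possible negative needs two missing items, the lowest score on the other seven, and a raw sum. Some outcome variation is therefore conceivable across all admitted surveys, so it would be too absolute to say that no odds ratio could ever be computed. But that variation would reflect missing items and not sleep, and the estimate would be uninformative.

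This rests on taking the item range and the cut-off at face value. If either is a misprint and the data were coded otherwise, the error lies in the text and the result may be sound; only the sponsor can establish that. It is still a wrong decision threshold for a named outcome and needs correcting. The effect of the missing rule for incomplete surveys is separate, and its size cannot be given.

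**What to change.** 1. Check the item coding and the cut-off against the instrument's published scoring.
2. Correct Objectives {7} and section {18a} so that item range, possible total and cut-off agree.
3. Confirm from the dataset and scoring code which coding and cut-off were used. If the printed ones were applied, rescore and rerun the binary model. If not, state what was applied.
4. State a rule for surveys with 7 or 8 items answered, and apply the cut-off to a total on the nine-item scale, for example the mean of the answered items × 9. Report how many surveys had 7, 8 and 9 items, by period.

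Step 4 does not replace steps 1 to 3: under the printed coding, scaling removes the only possible negative and makes the outcome constant.

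The cost is a text correction, a check of the scoring and, at most, one rerun of a model. No new data are needed.
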